#### Difference between intervention and control group

The main analysis concerns the difference between the intervention and control group at month 12. Data from the Diabetes Overview and general practice survey are analysed using simple, multiple, and logistic regression analyses. Analysis is done according to the intention-to-treat principle to test if the groups differ in terms of outcome measures. The analysis of survey data will take into account cluster effects using the intra-cluster correlation coefficient. Using *t*-test and *Χ*^2^ tests, depending on the outcome measure, it will be determined if randomization has resulted in systematically different groups. Survey data are tested to determine if questions or indices of questions are internally consistent (Cronbach alpha). In the regression analyses, control variables at the individual (e.g., seniority) and practice level (e.g., form and size of practice) are tested to determine its influence on survey outcomes.

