### Study aim and objectives

The overall aim of the project is to evaluate if virtual specialist conferences between endocrinologists and general practitioners about patients living with T2D is clinically effective and improves diabetes competences in general practice in comparison to usual practice. We distinguish between clinical objectives and competence and organization objectives in the following ways.

The primary clinical objective is to study if the intervention group compared to general practices receiving usual practice is superior in improving the percentage of patients with T2D and three types of co-morbidities on appropriate diabetes related medication:Ischemic heart disease and/or stroke being treated with glucagon-like peptide 1 receptor agonists (GLP1-RA) and sodium glucose cotransporter 2 (SGLT2) inhibitorMicro/macro-albuminuria being treated with Angiotensin-converting-enzyme-inhibitor (ACE) or angiotensin-2-receptorantagonist (AT2)Low-density lipoprotein (LDL) > 2.5 mmol/L being treated with Statins.

The secondary clinical objective is to study if the intervention group compared to the control group decreases the percentage of patients with type 2 diabetes and respectively:HbA1c < 58 mmol/LHbA1c < 53 mmol/LBlood pressure < 140 mmHgBlood pressure < 130 mmHgLDL > 2.5 mmol/LLDL > 1.8 mmol/L

The primary diabetes competence and organization objective is to study if general practitioners’ in the intervention group compared to the control group self-reports a higher degree of:Confidence and skills in managing type 2 diabetes in generalConfidence in managing type 2 diabetes and cardiovascular disease or heart failureConfidence in managing type 2 diabetes and blood pressureConfidence in managing type 2 diabetes and kidney diseaseConfidence in managing type 2 diabetes and cholesterol.

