### Blinding

Given the nature of this real-life intervention, general practitioners and endocrinologists cannot be blinded to their allocation to either the intervention or comparison arm. To limit influencing the behaviour of the control group, baseline information will not be collected from them and are not informed about the type of data that are collected for the main analysis at month 12. Researchers analysing the data will be blinded regarding which arm each general practice belongs to.

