### Data collection

Table 3 shows the study schedule including data collection points according to the SPIRIT guideline. Data are collected at month 0, 12, and 24 for the intervention group and month 12 and 24 for the control group.

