#### Clinical outcomes

Clinical outcomes will be collected from an IT-platform (DEN: “Diabetes Overblik”. ENG: “Diabetes Overview”) used by Danish general practices, which contains anonymous and aggregated diabetes data about patients (Additional file 3 shows screenshots). As per the agreement to participate in the study, each general practice assigns a contact person who will e-mail the screenshot of the data to the project group. Each general practice is renumerated for performing this activity. Data will also be obtained from nationwide Danish registries: The Clinical Laboratory Information System Research Database (LABKA), The Danish National Prescription Registry (DNPR), The Danish National Health Service Register (NHSR), The Danish Civil Registration System (CRS), and The Danish National Patient Register (NPR). Register data will be linked to the unique provider number of each general practice.

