### Sample and power calculation

The pragmatic nature of the RCT means that the sample size is determined by two contextual circumstances: a formal agreement with PLO-Aarhus and PLO-M to run the study in Aarhus Municipality (cf. above) where the total population of general practices was 100 and the fact that Danish general practices operate as private firms and thus decide themselves if they want to participate in a project. Based on these circumstances along with the study team’s research experiences with recruiting general practices, we used opinion-seeking to derive at the number of 30 general practices that were expected to participate.

We calculated the power for finding a significant difference between the intervention and control group on the three primary clinical outcomes using data from Danish registries and opinion-seeking within the study team. Additional file 5 shows the key parameters and the STATA command we used to calculate the following three power values:Power of 0.8870 for Primary clinical outcome 1: Percentage of patients with T2D and ischemic heart disease and/or stroke being treated with GLP1-RA and SGLT2 inhibitorPower of 0.9941 for Primary clinical outcome 2: Percentage of patients with micro/macro-albuminuria being treated with ACE or AT2Power of 0.9848 for Primary clinical outcome 3: Percentage of patients with LDL > 2.5 mmol/L being treated with Statins.

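### Cheap improvement: the month-12 comparison of the primary clinical outcomes has no baseline term, although registers the trial already links could probably supply one for both arms without contacting control practices

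*Protocol article*

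**What the plan says.** Under Difference between intervention and control group, the article states: "The main analysis concerns the difference between the intervention and control group at month 12". The data named for that analysis are the Diabetes Overview and the survey: "Data from the Diabetes Overview and general practice survey are analysed using simple, multiple, and logistic regression analyses". Control variables are described there for survey outcomes only.

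The schedule under Data collection gives the arms different time points: "Data are collected at month 0, 12, and 24 for the intervention group and month 12 and 24 for the control group". The Blinding section says of the control practices that "baseline information will not be collected from them". The reason given there, and again under the fourth limitation in the Discussion, is to avoid influencing how control practices behave.

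Under Data collection, Clinical outcomes, the article adds a second source: "Data will also be obtained from nationwide Danish registries". The list includes a laboratory database, the prescription registry and the patient register, and "Register data will be linked to the unique provider number of each general practice". Nothing limits this linkage to one arm. Under Sample and power calculation, power for the three primary clinical outcomes was computed "using data from Danish registries and opinion-seeking within the study team".

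**The concern.** The randomised units are practices, and about 30 are expected. With so few units, a practice's treatment percentage before randomisation may predict its month-12 percentage well, and using it would narrow the interval for the treatment effect. As scheduled, no such value exists for the control arm. The month-0 Diabetes Overview data from the intervention arm alone cannot serve as a covariate.

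The stated reason for having no control baseline concerns contact with the practices. A register extraction needs no contact, so that reason does not rule out a register baseline. Precision is also hard to buy in other ways: the number of practices is set by local agreements and willingness to take part, and the Discussion describes recruitment as difficult. Stratification (Assignment of interventions) uses the number of full-time GPs and location, not the level of treatment before the trial.

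**Working it through.** **Inputs from the article.** 30 practices, 15 per arm, 1:1 allocation. Stated power is 0.8870, 0.9941 and 0.9848 for primary outcomes 1, 2 and 3. The cut-off for each primary clinical outcome is 0.0167.

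**Assumed input.** r, the practice-level correlation between the baseline and month-12 percentages. The article gives no value, so a range is shown.

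**The plan's own figures.** The Bonferroni cut-off reproduces: 0.05/3 = 0.0167. The three powers cannot be reproduced, because the rates, effect sizes, intracluster correlation, cluster size and alpha are in Additional file 5, which is not at hand. The effect is therefore back-solved from the stated power for outcome 1.

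**Step 1, chance imbalance.** In units of the between-practice SD, the difference in mean baseline between two arms of 15 has SD √(2/15) = 0.365. The chance of an imbalance above 0.25 SD is about 49%, and above 0.5 SD about 17%. Both figures ignore any help from stratification.

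**Step 2, implied effect for outcome 1.** At two-sided alpha 0.05, z(0.975) + z(0.887) = 3.171, so d = 3.171 × 0.365 = 1.16 practice SD. Had the power been computed at 0.0167, the sum is 3.605 and d = 1.32. A baseline imbalance of 0.5 SD at r = 0.5 would shift the month-12 difference by 0.5 × 0.5 = 0.25 SD, about 22% of 1.16 (0.25/1.16).

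**Step 3, effect of adjustment.** The variance factor is 1 - r², and the number of unadjusted practices giving the same precision is 30/(1 - r²). Power comes from a simulation of 15 against 15 practices (20,000 runs, t critical values, alpha 0.05, d = 1.16). The simulation pays for estimating the slope.

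| r | Variance factor | Equivalent practices | Simulated SE ratio | Simulated power, outcome 1 |
|---|---|---|---|---|
| 0 | 1.00 | 30 | 1.02 | 0.85 |
| 0.3 | 0.91 | 33 | 0.97 | 0.88 |
| 0.5 | 0.75 | 40 | 0.88 | 0.93 |
| 0.7 | 0.51 | 59 | 0.73 | 0.99 |

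Unadjusted power in the same simulation is about 0.86, not 0.887, because t rather than normal critical values are used. Normal quantiles would give 0.91, 0.96 and 0.99 at r = 0.3, 0.5 and 0.7, which is slightly high for 30 units.

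**Step 4, the cut-off actually used.** If the stated 0.887 was computed at alpha 0.05 (not shown), power at 0.0167 is about 0.78 without adjustment and 0.82, 0.90 and 0.98 with it at r = 0.3, 0.5 and 0.7. These are normal-quantile figures and also run slightly high.

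**Step 5, outcomes 2 and 3.** Both have stated power above 0.98, so little power is left to gain. The benefit is a narrower interval: by the simulated SE ratios, about 3%, 12% and 27% narrower at r = 0.3, 0.5 and 0.7.

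**The case against.** A reader might infer that the unadjusted comparison is biased or invalid. It is not. Randomisation makes the month-12 difference unbiased, and a correct interval already allows for chance imbalance. Imbalance and lost precision are therefore one cost seen from two sides. Nor does the month-12 contrast contradict the primary objective, which asks whether the intervention "is superior in improving the percentage of patients with T2D": in a randomised comparison the difference in month-12 levels estimates the same effect as the difference in improvement.

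It is also tempting to say that the registers can certainly supply all three outcomes before randomisation. The article does not show this. It names the registers and the linkage, but gives no time window and no register definitions of the outcomes, and it says register data are used under licence. Their use in the power calculation suggests feasibility without proving it.

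Three further objections carry weight. The size of the gain rests on an assumed r. That r could be low if prescribing guidance moves fast, if membership of the LDL group changes between dates, or if register and Diabetes Overview definitions differ. Stratification by practice size and location may already remove part of the imbalance.

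The remaining objection is that covariates are commonly left to a separate analysis plan, and that multiple regression is already named. An adjusted model would indeed still estimate a month-12 difference. But the article does more than stay silent: it schedules month-0 data for one arm only and gives a reason for having none in the other. That decision can be judged as written, and its reason does not extend to register data.

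**Conclusion.** The point stands as a cheap improvement in precision, not as an error or a bias. The variance of the month-12 difference would be multiplied by 0.91, 0.75 or 0.51 at r = 0.3, 0.5 or 0.7, with a loss of about 2% in standard error if r is near 0. Outcome 1 has the most power to gain.

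This rests on three assumptions: that the linked registers can yield a practice-level value for each primary outcome before randomisation, that r is clearly above zero, and, for the power figures, that the effect implied by the stated power for outcome 1 is right. The imbalance figures are upper bounds to the extent that stratification helps.

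**What to change.** Provided the register licence and time window allow it:

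- Extract, for every randomised practice in both arms, a register-based practice-level value of each primary clinical outcome over one fixed window before randomisation.
- Under Difference between intervention and control group, prespecify that value as a covariate in the practice-level month-12 model for the corresponding outcome. Keep the unadjusted comparison as supportive.
- Reword the Blinding section and the fourth limitation in the Discussion to say that no baseline is collected by contact with control practices.

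The cost is one degree of freedom out of about 28 and a somewhat longer register extraction. Register definitions may differ from those of the Diabetes Overview. That would lower r and so the gain, but it would not bias the comparison, because the covariate is measured in the same way in both arms before randomisation.

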#### Missing data

By applying the above strategies of data collection (e.g., remuneration for providing data, sending reminders) and retention (e.g., general practices signing an agreement to participate), we expect to limit the risk of missing outcome data to a minimum. In case general practices leave the study, we will record the reason(s). To determine if it is relevant to deal with missing data by using multiple imputation (e.g., single value regression analysis), we will follow the recommendation by Jakobsen et al. [41] that the decision relies on being able to answer no to all of the following five key questions, i.e.;Is it valid to ignore missing data (rule of thumb: below 5% missing)?Too large proportions of missing data (rule of thumb: > 40%)?Is data only missing on the dependent variable?Is the missing completely at random assumption plausible?Is the missing not at random assumption plausible?

In case an answer is yes, we will use observed data only and then thoroughly discuss and report the extent of the missing data and the limitations.

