## Discussion

The intervention relies on randomization of general practices, thereby not targeting a certain type of general practice. The randomization allows for generalizing findings and the qualitative evaluation provides points of learning to GPs across the five Danish regions. The project results also have broader perspectives as the intervention can be applied to other chronic diseases or conditions where dialogue between the hospital and GPs is needed to support the latter in caring for their patients. The results and intervention are also expected to be applicable to other countries with a health system similar to the Danish such as the English NHS. The generalizability is moreover fostered by performing a process evaluation to assess the fidelity of the intervention alongside identification of organizational factors (e.g., how service is delivered) [42].

Given the design of the study, five major limitations apply. First, patient outcomes rely on data retrieved from an IT-platform (Diabetes Overview), and the precision of the outcomes thus depends on the quality of and reporting to the underlying database. Overall, data in Danish registries have high accuracy [46, 47]. To ensure data quality, the first introductory virtual conference serves an important aim and that is getting the GPs to review their list of patients with diabetes (i.e., enter or remove patients) by ensuring that those on the list have the correct diagnostic codes. When patients are registered correctly, data are automatically shown in the Diabetes Overview. The data will be provided by the participating GPs, a task for which they are remunerated, thereby ensuring availability of data.

Second, getting GPs to participate in research projects in Denmark can be difficult because they operate as private for-profit firms, and patient demands means they often work on a tight schedule [30]. Recruitment of GPs during the COVID-19 pandemic is even more challenging [48]. Nevertheless, our recruitment strategy in six steps (e.g., reimbursement and phone calling) are expected to facilitate recruitment. Third, we risk that only GPs participate who are particularly interested in diabetes, thereby resulting in a biased sample. By comparing the sample with the population of GPs and general practices in Aarhus Municipality, we will analyse how similar the sample is to the population.

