Fourth, GPs and endocrinologists cannot be blinded to their allocation status. To limit that the behaviour of the control group is influenced, baseline information will not be collected and they are not informed about the data we will collect at month 12. However, participants in the control group can on their own decide to improve the management of T2D by, for example, taking courses and thus move closer to the outcomes of the intervention group. The degree to which this is the case will be captured by asking about changes made during the past year. Fifth, common method bias [49] is considered a small potential risk in the study even though self-reported data (i.e., survey to GPs and practice staff) and administrative health data from the Diabetes Overview (i.e., screen shoots of the primary and secondary outcomes) are collected from the same data source. The risk is moreover considered small because the administrative health data is updated automatically, and the two types of data are collected at different points in time.

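### Register data listed for the clinical outcomes have no stated role in the main comparison or when a screenshot is missing, so a practice that sends none will almost always leave the intention-to-treat analysis

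*Protocol article*

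**What the plan says.** The Data collection section, under Clinical outcomes, describes two sources. The first is the Diabetes Overview, an IT platform showing aggregated data: "each general practice assigns a contact person who will e-mail the screenshot of the data to the project group". The second follows in the same paragraph: "Data will also be obtained from nationwide Danish registries", namely laboratory, prescription, health service, civil registration and patient registers. It adds: "Register data will be linked to the unique provider number of each general practice".

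The analysis section on the difference between the groups names one of these sources, together with the survey: "Data from the Diabetes Overview and general practice survey are analysed using simple, multiple, and logistic regression analyses". The same paragraph commits to intention-to-treat. The Discussion agrees on the source. It says that "patient outcomes rely on data retrieved from an IT-platform (Diabetes Overview" and describes the administrative data as "screen shoots of the primary and secondary outcomes".

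On practices that withdraw, the Missing data section says: "In case general practices leave the study, we will record the reason(s". Multiple imputation is considered only if five questions are all answered no. If any answer is yes, observed data only are used, and the extent of missing data and the limitations are reported. No register is mentioned in that section. The Blinding section states that "general practitioners and endocrinologists cannot be blinded to their allocation to either the intervention or comparison arm" and that no baseline information is collected from control practices.

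**The concern.** The screenshot exists only if a practice that knows its allocation is still cooperating at month 12. Register data do not require the practice to send anything. The plan obtains both but gives a stated analysis role only to the source that depends on cooperation.

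Two things are at stake. The comparison labelled intention-to-treat may in effect become a comparison of practices that sent a screenshot. And with about 15 practices per arm, each loss costs some power and, if related to both arm and outcome, shifts the estimated difference.

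**Working it through.** **1. Where the registers appear.** Data collection lists them for the clinical outcomes. Data management says how they are handled, and Data Availability says they are used under licence. The sample-size section used register data for planning. The section on the main comparison, the section on changes within each arm and the Missing data section name no register. Their role in analysing the primary outcomes is therefore unstated.

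**2. What the missing-data rule does with a missing screenshot.** Assume 30 practices, 15 per arm.
- One missing: 1/30 = 3.3%. This is below the 5% rule of thumb, so question 1 is answered yes and observed data only are used.
- Two missing: 2/30 = 6.7%. Question 1 is now answered no. But a missing screenshot removes only the outcome, so question 3 (missing only on the dependent variable) is answered yes, and again observed data only are used.
- Imputation is reached only if something besides the outcome is also missing and the other four answers are no. Control practices would still have no collected baseline to support it.

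**3. Power, as an illustration.** The Bonferroni cut-off reproduces: 0.05/3 = 0.0167. The stated powers (0.8870, 0.9941, 0.9848) cannot be rebuilt, because their inputs are in Additional file 5, which is not shown. Nor is it known which alpha was used or whether loss was allowed for. I therefore take each stated power as given, back out the implied signal under a normal approximation, and rescale it:

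- signal = z(1-alpha/2) + z(power)
- factor = sqrt[(2/15)/(1/k1 + 1/k2)]
- new power = Phi(signal x factor - z(1-alpha/2))

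Assume 3 intervention practices and 1 control practice are lost, so k1 = 12 and k2 = 14. The factor is sqrt(0.1333/0.1548) = 0.928. For outcome 1:
- alpha 0.0167: signal = 2.394 + 1.211 = 3.605; 3.605 x 0.928 - 2.394 = 0.952; power 0.829.
- alpha 0.05: signal = 1.960 + 1.211 = 3.171; 3.171 x 0.928 - 1.960 = 0.983; power 0.837.

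A milder loss of 2 intervention practices (13 v 15) gives 0.860 and 0.863. With 12 v 14, outcome 2 stays at about 0.985 and outcome 3 at about 0.967.

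**4. Bias, as an illustration.** Let the gap be the difference between the practices lost and those that stay in the intervention arm. The observed arm mean is then shifted by (share lost) x gap. With 3 of 15 lost and an assumed gap of 5 to 15 percentage points, the shift is 0.2 x 5 = 1 point to 0.2 x 15 = 3 points.

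In standardised terms, take the SD as that of the observed practice percentages, keep 12 v 14, and let the control loss be unrelated to outcome. Then SE = sqrt(1/12 + 1/14) = 0.393 SD.
- Gap of 1 SD: shift 0.2/0.393 = 0.51 SE. With no true effect, the two-sided rejection rate rises from 1.67% to about 3.2%, or from 5% to 8.0%.
- Gap of 0.5 SD: shift 0.25 SE, with rates of 2.0% and 5.7%.

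The loss patterns and gaps in steps 3 and 4 are assumptions; the documents give none.

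**The case against.** The strongest reply is that this argues from silence. The registers are listed under Clinical outcomes and licensed for this study, and the main analysis is not said to use the Overview exclusively. An analysis plan that is not shown may give them a role. That stands as a caution against saying that the registers will not be used. It does not settle the point, because the article itself states the analysis source and the missing-data rule, and following both as written removes the practice.

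Losses may also be few. Practices sign an agreement, name a contact person, are paid and receive up to three reminders, and the required act is one e-mail. A practice that skips conferences can still send its screenshot and be analysed as randomised. This stands and limits the likely size.

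A reader might go further in four ways that the documents do not support:
- That the register data are already in hand. The text says only that they will be linked.
- That every loss is avoidable. The article does not show that the registers can rebuild the type 2 diabetes population, which in the Overview depends on practices' diagnostic coding, or that register data may be used after a practice withdraws.
- That control practices are less able to send the screenshot because only the intervention arm has had the webinar by month 12. The platform is described as in use in Danish general practice, and all participants agree to supply data.
- That the registers should replace the Overview as the main source. That would change the definition of the primary outcomes, and reasonable statisticians would disagree about it.

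**Conclusion.** The point holds as a gap between the data-collection section and the two analysis sections. A second source is obtained for the clinical outcomes, but it has no stated role in the main comparison or when an outcome is missing. The missing-data rule then makes exclusion the near-certain result for a practice with no screenshot, which does not fit the intention-to-treat commitment.

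The size is modest and conditional. For the least-powered outcome, the assumed loss of four practices costs about 5 to 6 percentage points of power; the other two outcomes remain above 0.96. Bias requires loss related to both arm and outcome, and no document figure says that this will occur. The point deserves correction before analysis. It does not show that the planned result is invalid.

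**What to change.** Keep the Diabetes Overview as the main source. In the sections on the main comparison and on missing data, state that the three primary clinical outcomes will also be derived from the linked registers for every randomised practice, where consent and register permissions allow. Name this as the intention-to-treat sensitivity or fallback analysis to be reported whenever any month-12 screenshot is missing. Fix it before month-12 results are known, so that the choice of source cannot follow the results.

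Specify the register definitions in advance: how type 2 diabetes, each comorbidity or laboratory criterion, and treatment at month 12 are identified, and from which register. Confirm what may be used after a practice withdraws. Acknowledge that these definitions will not match the Overview exactly. The blood-pressure outcomes can stay on the Overview, since no listed register is described as holding them.

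The cost is wording, programming of the definitions and possibly a wait for register delivery. No data beyond those already planned are collected.
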